## Abstract

**Introduction:**

Idiopathic scoliosis is the most common spinal deformity in children. Treatment strategies aim to halt progression of the curve. Patients are treated mainly with thoracolumbosacral orthosis (TLSO) if indicated. This form of brace treatment has been shown to be cumbersome and tough on growing individuals. However, computer aided design and manufactured (CAD/CAM) braces might increase comfortability and ultimately outcome if compliance is improved. In a multicenter, randomized controlled trial, we aim to compare CAD/CAM designed Boston 3D-brace to standard Boston brace.

**Methods:**

Subjects: 170 previously untreated and skeletally immature children diagnosed with idiopathic scoliosis, aged 9–17 years of age (curve magnitude Cobb 25–40 degrees) will be included. Interventions: Both groups will receive a physical activity prescription according to the World Health Organization recommendations. Randomization will be performed 1:1 to a 3D CAD/CAM designed Boston 3D-brace or a standard Boston brace, both with prescribed daily wear time of 20 hours. Outcome: The subjects will participate in the study until curve progression or until skeletal maturity. The primary outcome variable is failure of treatment, defined as progression of the Cobb angle more than 6 degrees compared to the baseline x-ray. The progression is confirmed if seen on two consecutive standing spinal x-rays. Radiographs will be taken at each six-month follow-up. Secondary outcome measures include patient and clinical reported outcomes, including number of individuals requiring surgical intervention.

**Discussion:**

This study will show if efficacy in brace treatment can be improved with new brace designs.

**Trial registration:**

The protocol has been registered on ClinicalTrials.gov, identifier: NCT04805437.

## Introduction

Idiopathic scoliosis is the most common spinal deformity in children and adolescents with an estimated prevalence of 3% [1]. About one tenth of the children with scoliosis develop a deformity that requires treatment with brace or surgery with current treatment protocol. School screening programs in Sweden account for at least 200,000 children screened for scoliosis per year. Children with a suspected scoliosis are usually referred to orthopedic specialists for evaluation. Standard treatment consists of bracing 18–20 hours or more per day and gold standard in brace treatment is a rigid thoracolumbosacral orthosis (TLSO), aiming to halt curve progression by providing 3-dimensional (3D) correctional counterforces to the scoliosis curvature [2]. Previous literature on quality of life has suggested that brace treatment, being in many cases tough and cumbersome on adolescents, might have a negative impact on mental health and studies have also shown that patients surgically treated for idiopathic scoliosis are to a larger extent satisfied with management [3–5]. Outcomes of brace treatment depend to a large extent on wearing time [6]. Since many adolescents feel uncomfortable in the brace, it is of importance to combine efficacy and comfortability of the brace. In recent years, braces designed using computer-aided design and manufacturing system (CAD/CAM) have been developed, aiming to improve customization and comfortability for the patient. Using CAD/CAM might provide better 3D effect on the curvature rather than internal molded forms being inserted in the standard brace. Previous studies have shown promising results in producing lighter, more customized and efficient braces [7–10].

In a quadruple-blinded randomized controlled trial, we seek to compare CAD/CAM designed Boston 3D-brace to standard Boston brace in patients with moderate idiopathic scoliosis.

### The question at issue/hypothesis

We hypothesize that a CAD/CAM designed Boston 3D brace increases compliance and comfortability resulting in superior outcomes compared to the standard Boston brace.

## Methods

### Study design

This is a quadruple-blinded randomized controlled trial. The protocol has been registered on ClinicalTrials.gov, identifier: NCT04805437. Individuals who meet inclusion criteria will be asked for participation. After informed consent, randomization will take place. Currently, this study will be performed at Karolinska university hospital in Stockholm, Sweden. Further centers will be involved continuously. Fig 1 includes a flow scheme for the study.

**Fig 1 pone.0255264.g001:**
[figure not shown]
Flow scheme of patient recruitment and management.

Fig 2 illustrates SPIRIT checklist.

**Fig 2 pone.0255264.g002:**
[figure not shown]
SPIRIT 2013 checklist: Recommended items to address in a clinical trial protocol and related documents.

### Subjects

Patients referred to the participating clinics are consulted and examined by a health care provider specialized in spinal disorders. The magnitude of the scoliosis in the frontal plane is assessed by measuring the Cobb angle [11]. Upon inclusion, full spine frontal and sagittal radiographs, pelvic and hand radiographs will be taken. Up to three months old radiographs will be accepted. Prior or during the study, full spine Magnetic Resonance Imaging (MRI) may be done for all individuals at one occasion. The following inclusion criteria will be applied:

Skeletally immature patients. Sanders score ≤ 6 [12], Risser sign ≤ 2 [13] and menarcheal status not more than one year for females.Age 9–17 years of age at inclusion.Primary curve of 25–40 degrees Cobb angle.Scoliosis of idiopathic nature with no previous brace or surgical treatment.Apex of the primary curve at T7 or caudal.

### Boston 3D brace

A CAD/CAM designed Boston 3D brace will be designed to the patient’s individual type of scoliosis. In-brace radiographs will be performed after prescription. Reinforcement of the intervention will be performed in conjunction with reassessment every six months. Patients are encouraged to use the brace for a minimum of 20 hours per day and to also continue with physical activities for the entirety of the study. Compliance will be monitored with a thermal sensor (iButton DS1922L Thermochron Data Logger, Measurement Systems Ltd, United Kingdom) built in the brace that measures wearing time. The thermal sensor will be set to measure every hour.

### Standard Boston brace

A standard Boston brace will be designed to the patient’s individual type of scoliosis. In brace radiographs will be performed after prescription. Reinforcement of the intervention will be performed in conjunction with reassessment every six months. Patients are encouraged to use the brace for a minimum of 20 hours per day and to also continue with physical activities for the entirety of the study. Compliance will be monitored with a thermal sensor (iButton DS1922L Thermochron Data Logger, Measurement Systems Ltd, United Kingdom) built in the brace that measures wearing time. The thermal sensor will be set to measure every hour.

### Non-participants

Patients not willing to undergo randomization will be treated in accordance with local procedures. Standard TLSO brace treatment will be offered. Non-participants will be asked to answer the same questionnaires as the study cohort at the time when treatment is initiated. The radiological and clinical result of these patients will be obtained from the regular orthopaedic files and radiographs taken.

### End of study

The study primary endpoint will be reached when the participant reaches skeletal maturity, defined as less than 1.0 cm growth of body height in six months, or if the curve progresses more than 6 degrees, compared to the baseline radiograph, seen on two consecutive spinal standing radiographs. Curve progression will not lead to change of brace. In the event that a Cobb angle surpasses 50 degrees, patients will be offered surgical treatment. Follow-up is planned to occur at 2, 5 and 10 years after skeletal maturity including standing full spine frontal and sagittal radiographs.

### Ethical permit

This study has been ethically approved by the Swedish Ethical Review Authority (approved 2021-04-20. Diary number: 2020–06502).

### Randomization procedure

After assessment, patients fulfilling the inclusion and exclusion criteria will be asked to give written and signed consent for participation. If the patient is aged 15 years or less, parental consent is also required. Patients who decline participation will be followed and monitored as part of clinical routine.

Randomization will be done in a 1:1 ratio. Randomization will be performed using an online module available through the Swedish spine register (www.swespine.se). Randomization sequence have been prepared by an independent data manager (www.medscinet.com), which runs the register platform, and is not accessible for the researchers.

### Blinding

Patients, care provider, investigators and outcome assessors will be blinded to the type of brace prescribed. Orthotist and research nurse will know what type of brace the participant receives but will not tell the participant which type he/she has received. The brace will not be brought inside the examination room during follow-ups. Readings of the thermal sensor will only be handled by the research nurse. For both patient groups, the procedure with scanning and measuring prior to bracing, and delivery of the brace, will be identical at the orthotist.

### Outcome measurements

Primary outcome measure is change in the Cobb angle of more than 6 degrees from baseline to the radiographic follow-ups and confirmed on two consecutive radiographs, similar to a previous randomized trial from our group [14]. Radiographs will be taken every six months in conjunction with clinical follow-ups until skeletal maturity. During each follow-up, two independent experts blinded to the type of intervention will assess the radiographs to determine if progression has occurred. If progression is suspected, additional radiographs may be taken for verification, also at additional time points not being considered as regular follow-ups.

Secondary outcome measures recorded at baseline and every six months for the entirety of the study include angle of trunk rotation, as measured with Bunnell’s scoliometer [15], patient-reported outcomes as measured with Scoliosis Research Society-22r, EQ-5D-youth version, Visual Analogue Scale-pain (VAS-pain), the International Physical Activity Questionnaire (IPAQ) short form and the pictorial part of Spinal Appearance Questionnaire (pSAQ) and hours in brace. Patients eventually also requiring surgical treatment will be recorded.

At each follow-up additional questions regarding protocol fulfillment (own-perceived compliance of the treatment), patient satisfaction and adverse effects (such as skin issues, pain and discomfort caused by bracing) will be monitored.

### Data integrity

Data will be entered by the participant directly in an online module, or by paper format and then entered by the research staff.

### Data analysis

Data from the trial will be compared based on the ’intention to treat’ (ITT) principle. An (ITT) analysis means that all patients, regardless of non-compliance, loss to follow-up or drop-out, remain in the analysis of the group to which they were randomized [16]. Multiple imputation or maximum likelihood methods of missing data will be used in the ITT analysis. A sensitivity analysis will be performed comparing the ITT data against a per-protocol data exclusively from patients who complied with the study protocol. If a patient fails treatment and is offered another treatment, such as surgery, the Cobb angle at the moment of commencing this treatment will be considered in the secondary outcome analysis of Cobb angle. Categorical parameters will be compared by the Chi-square test. Continuous and discrete parameters will be measured using parametric or non-parametric tests (depending on skewness) for group comparisons. Individual variables (such as actual brace time, in-brace correction and maturity) will be tested for their association with treatment effect by adding a predictor × treatment group interaction term to a regression equation. Additionally, Kaplan-Meier survival analyses will be used to display the probability of more than 6° Cobb progression over time for both trials.

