### Power analysis

The end point failure of treatment is defined as an increase of the Cobb angle of at least 6° on two consecutive x-rays, when compared to the x-ray performed at time of inclusion. Based on a hypothesized failure rate of 2% in the 3D-brace group and 15% in the standard brace group [6] with 5% two-tailed significance level and 80% power and consideration for dropout of up to 20%, 85 individuals are required in each group.

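### The only test stated for the binary primary endpoint is unadjusted, so correction for chance imbalance in baseline Cobb angle and maturity is forgone, with at most a small gain in power

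*Protocol article*

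**What the plan says.** The Outcome measurements section of the protocol article defines a yes/no endpoint: "Primary outcome measure is change in the Cobb angle of more than 6 degrees from baseline to the radiographic follow-ups", confirmed on two consecutive radiographs. For outcomes of this type, Data analysis states one test: "Categorical parameters will be compared by the Chi-square test". Kaplan-Meier curves are there for display only. Regression has one stated use: individual variables, with actual brace time, in-brace correction and maturity as examples, "will be tested for their association with treatment effect by adding a predictor × treatment group interaction term to a regression equation". That looks for effect modification and does not adjust the main comparison.

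The Subjects section limits entry by primary curve (25–40 degrees) and by maturity (Sanders score, Risser sign, menarcheal status). It also says "Upon inclusion, full spine frontal and sagittal radiographs, pelvic and hand radiographs will be taken". Both variables are therefore available for every participant at inclusion. The End of study section ends participation at skeletal maturity or at confirmed progression. On allocation, the Randomization procedure section says "Randomization will be done in a 1:1 ratio" and names no stratification factor.

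**The concern.** Two baseline variables that could plausibly predict failure are collected on everyone but do not enter the main comparison. Maturity matters twice. It may predict progression, and a less mature child stays in the study longer, so an imbalance in maturity is also an imbalance in time at risk. A crude comparison of proportions ignores this.

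Few failures are expected, so a modest difference between the groups in curve size or maturity could shift the result. Neither the stated allocation nor the stated test would correct for it. An adjusted analysis introduced after the results are known would look post hoc, so the choice has to be fixed in advance.

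**Working it through.** **Inputs (Power analysis section).** "5% two-tailed significance level and 80% power"; "hypothesized failure rate of 2% in the 3D-brace group and 15% in the standard brace group"; "consideration for dropout of up to 20%, 85 individuals are required in each group".

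**1. The plan's own figure.** Two proportions, unpooled variance:

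n = (1.960 + 0.842)² × (0.02×0.98 + 0.15×0.85) / 0.13² = 7.849 × 0.1471 / 0.0169 = 68.3 per group.

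With 20% dropout, 68.3 / 0.8 = 85.4, so the stated 85 is reproduced. The sample size rests on an unadjusted comparison, which agrees with the stated test. The steps below use 68 per group (after dropout) and 85 (all randomised).

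**2. Expected failures.** 68 × (0.02 + 0.15) = 11.6 and 85 × 0.17 = 14.5 in total. The 3D group contributes 68 × 0.02 = 1.4 at the lower figure, and the chance that it has none is 0.98^68 = 25%.

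**3. The Chi-square test as stated.** Power at 2% vs 15% is 78.2% (normal approximation) or 84.1% (exact binomial) with 68 per group, and 86.6% or 90.6% with 85. Exact type I error at a common rate of 8.5% is 5.2% (68) and 4.8% (85). The test does what the plan asks of it.

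**4. Adjusting for two baseline covariates.** The article gives no association between either variable and failure, so strength is assumed as an odds ratio (OR) per SD, the same for two independent standardised covariates. Marginal rates are held at 2% and 15%. The adjusted test is the logistic score test. With p the fitted risk from the model without brace, U = Σ t(y − p) over children, where t marks the 3D group. U² divided by its variance given the covariates is referred to Chi-square on 1 df. There were 3,000 simulated trials per setting (Monte Carlo SE about 0.7 points).

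| OR per SD | 68 per group: Chi-square / adjusted | 85 per group: Chi-square / adjusted |
|---|---|---|
| 1.0 | 84.1% / 83.6% | 89.8% / 90.2% |
| 1.5 | 83.0% / 83.4% | 90.7% / 91.4% |
| 2.0 | 84.1% / 86.1% | 91.0% / 92.6% |
| 2.7 | 83.5% / 88.0% | 90.0% / 94.2% |

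The change runs from −0.5 to +4.5 points. A separate simulation gave about −1 to +4.5.

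**5. Type I error of the adjusted test.** At 8.5% in both groups and 68 per group, the score test gave 4.9–5.3% against 5.0–5.1% for Chi-square. The separate simulation gave 5.2–5.7% against 5.2–5.5%. The ordinary likelihood-ratio version gave 5.4–6.1%, which is slightly too liberal.

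**6. Why the form of the test matters.** Firth-penalised logistic regression with the same two covariates was simulated at 68 per group (2,000 trials per setting).

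| OR per SD | Chi-square | Firth penalised likelihood-ratio | Firth Wald |
|---|---|---|---|
| 1.5 | 83.8% | 82.5% | 75.3% |
| 2.0 | 84.9% | 84.8% | 77.2% |
| 2.7 | 85.4% | 87.5% | 81.5% |

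Another run put the Firth likelihood-ratio test 1 to 3 points below Chi-square at OR 1.0 to 2.0, and 2 to 3 points above it at 2.7. Wald inference costs about 4 to 8 points.

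**7. Chance imbalance.** Combine the two covariates into one baseline risk score. With 68 per group, the difference in group means has SD √(2/68) = 0.171, so a difference beyond 0.25 SD in either direction occurs in about 14% of trials. Suppose the 3D group is by chance about 0.30 SD worse. Unadjusted power then falls from about 84% to 79%, 74% or 68% at OR 1.5, 2.0 or 2.7. If the 3D group is equally favoured and there is no true effect (15% in both groups), the chance of a false result in its favour rises from about 2.5% to 5%, 7% or 8%.

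**The case against.** The strongest reply is that nothing here is in error. A Chi-square test of two randomised proportions is valid, the trial was sized for it, and its power exceeds 80% by exact calculation. Randomisation makes the comparison unbiased in expectation, and the nominal 5% already averages over chance imbalances. All of this stands. The figures in step 7 are conditional on an unlucky allocation and do not show that the test fails overall. Two covariates also cannot remove every imbalance.

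A reader might infer that planned power is lost. It is not; only a possible gain is forgone. A reader might also scale the variance by 1 − rho² with rho = 0.5 and infer that power would rise from 78% to 89%. The article does not support that. It gives no correlation, and its entry limits narrow both variables. The approximation also starts from 78%, where exact power is about 84%.

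The next reply is that a condensed article may leave covariates and strata to a fuller document. This stands in part. The article does not call Chi-square the primary analysis in so many words, and its silence on strata is no fault in itself. But it does state a test for categorical outcomes, that test has no covariates, and no other stated comparison fits the primary endpoint.

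Last, modelling 12 to 14 events is fragile, and penalised regression can do worse than Chi-square. Step 6 confirms this. It limits the form of the remedy but does not remove the reason for one.

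**Conclusion.** The point holds as a recommended improvement. On the article's text, the primary comparison is unadjusted, although baseline Cobb angle and maturity are known for all and maturity sets time at risk. What is forgone is correction for chance imbalance in these two variables, plus about 0 to 4.5 points of power. The gain is negligible, or about 1 point negative, if the covariates are weakly prognostic. It reaches 4 points or more only near an OR of 2.7 per SD for each.

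These figures rest on the plan's 2% and 15%, on 68 to 85 analysed per group, and on two independent, normally distributed covariates of assumed strength. They do not show that the stated test is invalid or the trial underpowered.

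**What to change.** In Data analysis, name as the primary comparison a logistic-model score test of randomised brace, adjusted for baseline Cobb angle (continuous) and one baseline maturity measure, such as the Sanders score. Allow no other covariates, and do not use Wald inference. Report the effect as a standardised (marginal) risk difference with a 95% confidence interval. Use Firth penalisation only if separation makes it necessary for estimation. Keep the unadjusted Chi-square test as a supportive analysis. Settle this before the allocation is unblinded.

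The change needs no new data, visits or participants. Its costs are a model that must stay at two covariates because so few failures are expected, no real gain in power if those covariates prove weak, and a result slightly less simple to present than a 2×2 table.

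### Continuous secondary outcomes are compared by tests chosen on observed skewness, with no stated use of the baseline values collected for most of them

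*Protocol article*

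**What the plan says.** The Data analysis section of the protocol article gives one sentence on comparing the arms for non-categorical outcomes: "Continuous and discrete parameters will be measured using parametric or non-parametric tests (depending on skewness) for group comparisons". Regression appears in the same paragraph, but for another purpose. Variables such as brace time, in-brace correction and maturity are to be tested as effect modifiers "by adding a predictor × treatment group interaction term to a regression equation".

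Outcome measurements sets the schedule: "Secondary outcome measures recorded at baseline and every six months for the entirety of the study include angle of trunk rotation". The list continues with SRS-22r, EQ-5D-Y, VAS-pain, IPAQ short form, pSAQ and hours in brace. The Cobb angle is also a secondary outcome and has a baseline radiograph. For patients who fail and are offered another treatment, "the Cobb angle at the moment of commencing this treatment will be considered in the secondary outcome analysis of Cobb angle".

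On missing data, the section says: "Multiple imputation or maximum likelihood methods of missing data will be used in the ITT analysis".

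**The concern.** Three features of the stated method fit the data poorly.

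- **The test depends on the data.** Skewness, once seen, decides between a comparison of means and one of ranks. These answer different questions, and the answer may switch from one outcome or visit to the next. No threshold or rule is given.
- **No use of baseline is stated.** Most of these scales have a pre-treatment value that is likely to predict the later one. Using it in the comparison gains precision at almost no cost.
- **One missing-data option does not fit.** Maximum likelihood handles missing values through a model for the outcome, and a t-test or rank test does not supply one.

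Precision on these scales matters because the sample size rests on the binary endpoint alone. The Discussion and Summary nevertheless intend to draw conclusions on comfort and tolerability, to which the patient-reported scales contribute.

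**Working it through.** **Inputs from the protocol article (Power analysis).** The "hypothesized failure rate of 2% in the 3D-brace group and 15% in the standard brace group", two-sided 5% level, 80% power, dropout up to 20%, 85 per group.

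**The plan's own figure.** With the unpooled formula for two proportions, n = (1.960 + 0.842)² × (0.02 × 0.98 + 0.15 × 0.85) / 0.13² = 68.3 per group. Dividing by 0.80 gives 85.4, so the stated 85 is reproduced. It depends only on the binary endpoint, and nothing below alters it. The number evaluable after the planned dropout is 85 × 0.80 = 68 per arm.

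**Assumption.** The article gives no standard deviation or correlation for any continuous outcome. Let r be the correlation between baseline and follow-up, with equal variance at both times. The main range is r = 0.5 to 0.7, and 0.3 to 0.8 is also shown. Variances are relative to a comparison of raw follow-up values (= 1).

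- Change from baseline: 2(1 − r)
- Baseline-adjusted regression (ANCOVA): 1 − r²
- ANCOVA relative to change scores: (1 − r²) / [2(1 − r)] = (1 + r)/2

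| r | Change score | ANCOVA | ANCOVA saving vs raw | ANCOVA saving vs change | Raw-value n per arm matching ANCOVA with 68 |
|---|---|---|---|---|---|
| 0.3 | 1.40 | 0.91 | 9% | 35% | 68/0.91 = 75 |
| 0.5 | 1.00 | 0.75 | 25% | 25% | 68/0.75 = 91 |
| 0.7 | 0.60 | 0.51 | 49% | 15% | 68/0.51 = 133 |
| 0.8 | 0.40 | 0.36 | 64% | 10% | 68/0.36 = 189 |

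**Detectable difference.** With 68 per arm and raw values, 80% power is reached at (1.960 + 0.842) × √(2/68) = 0.48 SD. With ANCOVA this is multiplied by √(1 − r²): 0.42 SD at r = 0.5 and 0.34 SD at r = 0.7. With change scores it is multiplied by √[2(1 − r)]: 0.48 SD and 0.37 SD.

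**Power for a true difference of 0.48 SD.** It is 80% with raw values. For r = 0.3, 0.5, 0.7 and 0.8, ANCOVA gives 84%, 90%, 98% and 99.7%, and change scores give 66%, 80%, 95% and 99%. ANCOVA is better than both at every r shown.

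**Missing-data options against test types.**

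- Multiple imputation with a parametric mean comparison is coherent: the estimates pool by Rubin's rules.
- Multiple imputation with a rank test has no standard pooling under those rules.
- Maximum likelihood with either simple test has no model to work through.

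The text therefore permits combinations that cannot be carried out as written, alongside one that can.

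**The case against.** The strongest reply is that the sentence is short and open. It does not say that the tests are unadjusted or applied to raw follow-up values. They could be run on change from baseline, and a parametric test could include ANCOVA. Covariates and time points are commonly left to a statistical analysis plan, which is not shown. This stands in part. A reader might infer that baseline data are thrown away, but the article does not establish that. What it does state is a test chosen on skewness, with regression mentioned only for interactions. Even on the generous reading of change scores, adjustment is more precise.

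A reader might also infer that dropout will bias these comparisons. Follow-up does end at different times ("The subjects will participate in the study until curve progression or until skeletal maturity"). But the article keeps every randomised patient in the analysis and provides for missing data, so a comparison of observed values only is not what it describes. With complete data, chance baseline imbalance is not bias in a randomised comparison.

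Three further points stand:

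- A rank test can carry a Hodges-Lehmann estimate with an interval, so it does not rule out an effect estimate. The article does not state one.
- Multiple imputation, the first option named, works with a mean comparison, so the mismatch is partial.
- Brace hours, satisfaction and brace-related adverse effects have no meaningful pre-brace value. Baseline adjustment cannot help them, and they carry much of the compliance and comfort message.

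**Conclusion.** The point holds as a matter of precision and of a method fixed badly, for secondary outcomes only. The choice of test is data-driven and can move between means and ranks. No use of baseline is stated for comparing the arms, and maximum likelihood has no model to act through.

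With 68 evaluable per arm and r between 0.5 and 0.7, baseline adjustment lowers variance by 25% to 49% against raw follow-up values, as if 91 to 133 per arm had been studied. Against change scores the saving is 25% to 15%. These sizes rest on assumed correlations and equal variances, and the article does not say which comparator it intends. Neither the primary analysis nor the 85 per group is touched.

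**What to change.** Replace the sentence on continuous parameters along these lines:

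- Each continuous secondary outcome with a baseline value is compared between arms by a regression model adjusted for that value, and the adjusted difference is reported with its 95% CI.
- The model is ANCOVA at a pre-specified time point. If maximum likelihood is the chosen missing-data method, it is a likelihood-based mixed model over visits. State which of the two missing-data methods applies.
- Skewness is handled by a pre-specified transformation or by robust or bootstrap standard errors, not by switching tests on the observed data.
- The existing analysis rule for the Cobb angle when another treatment starts is kept.
- Simple comparisons remain for outcomes without a meaningful baseline (brace hours, satisfaction, adverse effects). The new wording should still name a method for discrete parameters, which the present sentence also covers.

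The cost is a change of wording and slightly more analysis work. No further patients, visits or measurements are needed. The change should be fixed before unblinding.

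### Two of the three named effect modifiers, brace time and in-brace correction, arise after randomisation, so their interaction tests cannot show who benefits; the per-protocol set has a related limit

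*Protocol article*

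**What the plan says.** The Data analysis section of the protocol article makes ITT the basis of comparison. On effect modification it says: "Individual variables (such as actual brace time, in-brace correction and maturity) will be tested for their association with treatment effect", to be done "by adding a predictor × treatment group interaction term to a regression equation". It also plans a sensitivity analysis that sets the ITT result against "per-protocol data exclusively from patients who complied with the study protocol".

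Other sections show what kind of variables these are:

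- **Hypothesis section:** the 3D brace "increases compliance and comfortability resulting in superior outcomes compared to the standard Boston brace".
- **Introduction:** CAD/CAM design may act better on the curve in three dimensions.
- **Two brace sections:** wearing time is logged by a sensor built into the brace and is the measure of compliance. In-brace radiographs follow prescription of the brace.
- **Outcome measurements:** hours in brace is a secondary outcome.
- **Discussion:** low wear is linked to treatment failure.
- **Subjects:** Sanders and Risser stage are assessed for eligibility.

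**The concern.** A predictor-by-treatment interaction describes who benefits when the predictor is fixed before allocation. Patients at a given level of the predictor are then still a randomised comparison. Brace time and in-brace correction do not meet that condition. A child who reaches a given number of hours in a more comfortable brace need not resemble a child who reaches the same hours in a less comfortable one. Holding hours fixed also removes the part of the benefit that the trial expects to come from added hours. As written, hours in brace is both an outcome of the brace and a modifier of its effect.

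The per-protocol set raises a related problem. Compliance is measured as wearing time. If the 3D brace changes wearing time, the compliers in the two arms are selected differently.

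At stake is how the secondary results are read. A statement that the braces do not differ once wear time is accounted for could follow by construction, even if the 3D brace worked exactly as hypothesised.

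**Working it through.** **1. The plan's own figure.** Inputs from Power analysis and Randomization procedure: "hypothesized failure rate of 2% in the 3D-brace group and 15% in the standard brace group", "5% two-tailed significance level and 80% power", "consideration for dropout of up to 20%, 85 individuals are required in each group", and 1:1 allocation.

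Unpooled normal approximation:

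n = (1.960 + 0.842)² × (0.15×0.85 + 0.02×0.98) / 0.13² = 7.849 × 0.1471 / 0.0169 = 68.3, so 69 per arm.

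With 20% dropout, 69/0.8 = 86.25, so 87, which is within two of the stated 85. The point made here does not change this figure.

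**2. Timing and role of each variable**

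| Variable | When known | Role given by the article |
|---|---|---|
| Maturity (Sanders, Risser) | At inclusion | Eligibility; valid modifier at its baseline value |
| Brace time | After delivery, by sensor | Hypothesised route of effect; also a secondary outcome |
| In-brace correction | Radiograph after prescription | Plausible route of effect (Introduction) |

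**3. Illustration at the article's failure rates.** The article gives no relation between hours and outcome, so everything below except 15% and 2% is assumed.

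- U is an unmeasured standard normal trait.
- Standardised hours: h = −a·U + e + δ·T, where T = 1 for the 3D brace and Var(e) = 1 − a².
- logit(failure) = c + k·U − h. There is no direct brace effect.
- c is set so that the standard arm fails at 15%. δ is set so that the 3D arm fails at 2%.
- 2,000,000 patients. Logistic models with T, centred h and T×h are fitted on 400,000.

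The ITT risk difference is −13 points and the unadjusted odds ratio is 0.11–0.12 throughout. The per-protocol columns give risk differences in points, keeping patients above the standard arm's median hours or above +1 SD.

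| a, k | Brace OR at mean hours | Interaction OR | Per-protocol, median cut | Per-protocol, +1 SD cut |
|---|---|---|---|---|
| 0, 0 | 0.99–1.03 | 1.00–1.01 | −4.36 | −1.53 |
| 0, 1 | 0.93–0.95 | 0.92 | −5.07 | −1.87 |
| 0.3, 1 | 1.77–1.99 | 0.90–0.91 | −3.35 | −0.57 |
| 0.6, 1 | 4.20–4.33 | 0.91–0.93 | −1.82 | +0.27 |
| 0.6, 1.5 | 9.13–9.28 | 0.88–0.90 | −1.25 | +0.76 |

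The required shift δ is 2.3 to 3.0 SD of hours. That follows from sending the whole 15%-to-2% effect through hours at this slope; it is not a forecast.

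**4. Smaller true effect, same model.** At 15% vs 8% the ITT risk difference is −7 points and the unadjusted OR 0.49. With a = 0, k = 0 the brace OR at mean hours is 0.99 and the median-cut per-protocol difference −1.42 points. With a = 0.6, k = 1 they are 1.63 and +0.24 points.

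**5. A second set of assumptions, in hours.** Wear = 14 + 2T + 3U + N(0, SD 3); logit(failure) = −2.0 − 0.15(wear − 14) − 0.5U.

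- ITT failure is 15.8% vs about 12.6%, OR 0.77.
- With wear and its interaction in the model, the brace OR is about 1.18 and the interaction OR 1.00.
- Among those wearing at least 16 hours (32% vs 50% of the arms), failure is about 4.9% vs 5.2%. The 16-hour cut is an assumption; the article states none.

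**6. Reading.** Erasing the adjusted brace effect needs only full mediation. Reversing it needs an unmeasured trait that affects both wear and progression. In these models, reversal of the per-protocol contrast also needs a strict cut or a smaller true effect.

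**The case against.** The strongest reply is that the article plans to test the interaction term, and in these simulations that term stays near 1 (0.88–1.01). The distorted figure is the brace coefficient at a given wear time, which the article does not say it will report. This stands. A reader might infer that the planned test would itself erase or reverse the effect, or that it would suggest the brace works only in compliers. Neither is supported: the interaction is close to null, and in step 5 compliers show no benefit. What remains is that the test, whatever its result, does not compare randomised groups.

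Other objections also hold in part:

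- Maturity is in the same sentence and is a legitimate modifier, so not all the interaction tests fail. The list is only illustrative.
- Per-protocol beside ITT is common practice, and a compliance cut-off may properly sit in the full protocol or analysis plan. Nothing says the set selects on in-brace correction. The label still matters, because a sensitivity analysis should address the same question as the ITT analysis.
- Brace hours are already a secondary outcome, so comparing them between arms is already planned.
- A reader might add that the interaction is barely estimable, since at 2% failure and 68 per arm (85 × 0.8) the chance of no 3D failures is 0.98^68 = 25%. That presumes a binary-endpoint model. The article says only that a regression is used and does not fix the outcome.

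**Conclusion.** The point holds in limited form. Brace time and in-brace correction are consequences of the allocated brace on the article's own reasoning, so their interactions with group cannot identify who benefits. Any brace effect read from such a model can be attenuated or, with unmeasured confounding, reversed. At the article's failure rates, an OR of about 0.12 becomes about 1.0 under full mediation and 1.8–4.3 with moderate confounding (a = 0.3 to 0.6, k = 1). A per-protocol difference can shrink from −13 points to between −4.4 and +0.3 over (a, k) = (0, 0) and (0.6, 1). These sizes depend on an assumed slope, full mediation and the strength of U; they show what is possible and do not predict what will occur.

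The per-protocol result answers a different, selected question and is not a robustness check on ITT. A reader might infer that the main result is at risk. It is not: the primary ITT comparison and the sample size are untouched. This is a correction to subsidiary analyses.

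**What to change.** Amend the Data analysis section as follows:

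- Limit interaction tests to variables fixed at baseline, for example Sanders or Risser stage at inclusion, baseline Cobb angle, age and curve apex. State that maturity means its baseline value.
- Keep the planned between-arm comparison of brace hours and add in-brace correction to it.
- Examine the link of both variables to progression only in an exploratory mediation analysis, with stated assumptions and adjustment for baseline confounders.
- Report the per-protocol result as supplementary to ITT and no longer as a sensitivity analysis.

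The cost is a few sentences and a small amount of extra exploratory analysis. No new patients or visits are needed.
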